## Abstract

Background: Heart rate variability (HRV) could have independent and critical prognostic values in patients admitted for ST segment elevation myocardial infarction (STEMI). There are limited data in the literature regarding HRV assessment in STEMI setting. Thus, we aim to investigate the potential correlations between HRV and adverse outcomes in a contemporary cohort of patients presenting with STEMI undergoing primary percutaneous coronary intervention (PCI). Methods: We will perform a prospective, observational cohort study in a single healthcare center. Adult patients aged ≥18 years presenting with STEMI in sinus rhythm will be enrolled for primary PCI within 12 h from symptoms onset. Time domain, frequency domain, and nonlinear HRV parameters will be measured using a medically approved wrist-wearable device for 5 min segments during myocardial revascularization by primary PCI. Additional HRV measurements will be performed one and six months from the index event. The primary composite outcome will include all-cause mortality and major adverse cardiovascular events (during the hospital stay, one month, and one year following admission). Several secondary outcomes will be analyzed: individual components of the primary composite outcome, target lesion revascularization, hospitalizations for heart failure, ventricular arrhythmias, left ventricular ejection fraction, and left ventricular diastolic function. Conclusions: Our study will enlighten the reliability and usefulness of HRV evaluation as a prognostic marker in contemporary patients with STEMI. The potential validation of HRV as a risk marker for adverse outcomes following STEMI will ensure a background for including HRV parameters in future risk scores and guidelines.

## 1. Introduction

Ischemic heart disease represents the leading global cause of death, owing to a higher prevalence of risk factors, such as arterial hypertension, diabetes mellitus, metabolic syndrome, and aging [1]. Hence, ischemic heart disease patients with an increased risk of adverse outcomes should be identified early to ensure a close follow-up and a timely therapeutic intervention.

In the case of patients with ST segment elevation myocardial infarction (STEMI), the European Society of Cardiology (ESC) guidelines advocated for early assessment of short- and long-term risks of adverse events [2]. In this regard, the Global Registry of Acute Coronary Events (GRACE) score was endorsed to identify high-risk patients [2,3]. Heart rate variability (HRV) is an indirect marker of autonomic nervous system function. To date, HRV proves to be an excellent prognostic element for mortality in patients with acute myocardial infarction or end-stage kidney disease [4,5]. However, none of the existing risk scores is perfect in predicting subsequent worse outcomes following STEMI. Therefore, the ability of HRV to increase the prediction power of current clinical models in STEMI is a matter of further research.

In addition to clinical, biological, and imagistic parameters recommended by the guidelines for risk stratification, HRV could have a significant and independent prognostic value in STEMI patients [6]. HRV represents the fluctuation in time of RR intervals, reflecting the balance between sympathetic and parasympathetic autonomic nervous systems [7]. In addition to neural activities, respiratory rate could also influence HRV measurements [8,9]. In addition, different respiratory biofeedback techniques were developed to modulate HRV parameters [10]. HRV should not be regarded as a single parameter, as it could be assessed by different time domain, frequency domain, and nonlinear measurements [11].

An early study revealed an association between HRV and mortality in patients with acute myocardial infarction (AMI), including those treated with thrombolysis (*p* = 0.028) [4]. In a more recent trial involving STEMI patients (with reperfusion therapy), time domain HRV measurements were associated with all-cause mortality [12]. However, there were no documented differences in HRV parameters regarding other end-points, including cardiac mortality and major clinical events [12].

Thus, the relevance of HRV assessment in a contemporary cohort of patients presenting with STEMI should be investigated, especially in the era of the new generation of drug-eluting stents.

Although most studies measured HRV parameters during 24 h electrocardiographic monitoring, some parameters are validated for a shorter time interval (2–5 min) [7,11]. This is of particular interest, as wearable devices were developed to provide (short-timed) HRV data and already received CE marks for medical use [13,14,15]. As far as we know, the utility of HRV assessment using wearable devices in STEMI patients was never investigated in clinical studies.

Therefore, we will conduct a single-center, prospective, observational cohort study to investigate the prognostic role of HRV recordings in patients presenting with STEMI revascularized by primary percutaneous coronary intervention (PCI).

## 2. Materials and Methods

We designed a protocol of observational, prospective cohort study according to STROBE statement (see Table S1), in which patients with STEMI will be enrolled [16]. At least 200 consecutive patients who meet inclusion criteria referred to the catheterization laboratory from the Institute of Cardiovascular Diseases “[name]M. Georgescu” will be analyzed. The study protocol was registered in the ClinicalTrials.gov database (NCT05098977) and was approved by the Ethics Committee of the Institute of Cardiovascular Diseases “[name]M. Georgescu” in Iasi, Romania.

Interventional studies involving animals or humans, and other studies that require ethical approval, must list the authority that provided approval and the corresponding ethical approval code.

### 2.1. Study Objectives

The objectives of our study are: (1) HRV measurement in patients presenting with STEMI revascularized by primary PCI using a wearable medical device; (2) Correlation assessment between HRV and short- and long-term adverse clinical events, including different subgroups of patients (chronic kidney disease, diabetes mellitus, elderly); (3) Development of a registry which will include HRV parameters measured in a contemporary cohort of patients with STEMI.

### 2.2. Eligibility Criteria

We defined several inclusion criteria which will be applied for each patient:(1)Age ≥ 18 years;(2)Patients in sinus rhythm;(3)STEMI diagnosis referred for primary PCI within 12 h from symptoms onset;(4)Patients who agree to participate in the study and sign the informed consent.

In addition, we pre-specified key exclusion criteria, which also encompassed factors interfering with RR intervals and HRV parameters:(1)Patients who are unable to sign the informed consent;(2)Atrioventricular block of any degree or sinus node dysfunction;(3)Atrial fibrillation;(4)Paced ventricular rhythm;(5)Frequent premature supraventricular or ventricular contractions;(6)Treatment with positive inotropic or chronotropic drugs;(7)History of myocardial infarction or myocardial revascularization (PCI or coronary artery bypass graft surgery—CABG);(8)Patients who refused to participate in the study.

STEMI will be defined according to the fourth universal definition of myocardial infarction [17].

### 2.3. HRV Parameters Measured

We will measure HRV parameters recommended by the ESC and the North American Society of Pacing and Electrophysiology guidelines [7]:

(1)Time domain parameters: standard deviation of all NN intervals (SDNN), HRV triangular index, the standard deviation of the average NN interval over short time divisions (SDANN), and the square root of the mean squared differences of consecutive NN intervals (RMSSD);(2)Frequency domain parameters: low-frequency power (LF), high-frequency power (HF), and LF/HF ratio.

Additionally, some nonlinear HRV parameters will be evaluated, such as SD1, SD2, SD2/SD1, approximate entropy, and sample entropy.

HRV will be measured in addition to medical and interventional therapy for myocardial infarction according to the latest ESC guidelines focused on STEMI [2]. HRV will be assessed using a medically approved wrist-wearable device (E4 wristband from Empatica, CE certified) for 5 min segments during myocardial revascularization by primary PCI (before and after revascularization). The E4 device will be placed on the non-dominant hand, with the case tightener on the top of the wrist. The validity of HRV measurement using an Empatica E4 wristband was previously confirmed in a clinical study [13]. Raw data regarding heart rate and HRV (interbeat interval data) will be extracted from the wristband and further analyzed using Kubios software. Among available E4 wristband sensors, photoplethysmography will be used to derive interbeat interval data from blood volume pulse analysis. The blood volume pulse signal has a sampling rate of 64 Hz (resolution 1/64 s) as specified by the manufacturer. All HRV parameters of interest (including frequency domain and nonlinear parameters) will be automatically calculated using Kubios software [18]. Moreover, eventual artifacts in raw data collection will be corrected using a very low threshold algorithm (0.45 s) in Kubios to avoid significant HRV parameters deformation. Additional HRV measurements will be performed after the index event (at one and six months).

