### 2.5. Outcomes and Follow-Up

The primary composite outcome will include all-cause mortality and major adverse cardiovascular events (MACE). MACE will include cardiac mortality, fatal and non-fatal myocardial infarction, unplanned target vessel revascularization (TVR), and stroke (ischemic or hemorrhagic).

In addition, several secondary outcomes will be analyzed: (a) all-cause and cardiac mortality; (b) fatal and non-fatal myocardial infarction; (c) unplanned target vessel revascularization; (d) target lesion revascularization (TLR); (e) stroke; (f) hospitalizations for heart failure; (g) ventricular arrhythmias; (h) LVEF and left ventricular diastolic function. Moreover, the primary composite outcome will be evaluated in a high-risk subgroup of patients, such as elderly patients or those with diabetes mellitus/chronic kidney disease.

TVR will be defined as new stenosis requiring PCI or CABG in another part of the coronary artery treated at the index event. TLR will include unplanned PCI or CABG for the same lesion revascularized during primary PCI. LVEF will be measured using two-dimensional transthoracic echocardiography (Simpson methods). At least E/A or E/e prime ratios will be calculated for left ventricular diastolic function. Ventricular arrhythmias will be defined as ventricular fibrillation or sustained ventricular tachycardia documented at electrocardiographic monitoring. The primary composite outcome and secondary outcomes will be evaluated during the hospital stay, at 1 month and 1 year following admission for STEMI. All data regarding the outcomes will be collected from secure medical records.

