### 2.6. Participation Timeline

The expected duration of the study is three years following ethical approval by the local ethical review committee. As a first step, eligibility criteria will be analyzed at patients’ admission to the catheterization laboratory. Patients will be enrolled if all inclusion criteria will be fulfilled. During primary PCI procedure, HRV will be continuously monitored using a wearable device, which will be further analyzed offline using Kubios software. Additionally, at the index procedure demographic data, time to primary PCI in relation to chest pain onset; data regarding comorbidities and cardiovascular risk factors; and specified clinical, biological, and echocardiographic parameters will be collected.

During the hospital stay, patients will be re-evaluated echocardiographically and pre-discharge LVEF will be recorded. All outcomes of interest will be reported at this first time point in order to analyze a possible correlation between previously measured HRV parameters and short-term adverse events.

At 1 month and at 12 months after the index event, HRV will be re-assessed. In addition, in these time frames, clinical and echocardiographic data will be collected. Primary and secondary outcomes will be reported and an eventual correlation with HRV measured during primary PCI, as well as after 1 month and 12 months, will be analyzed.

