**Interventions**					
Demographic data		X			
Time to PCI		X			
Comorbidities		X			
Cardiovascular risk factors		X			
Blood collection		X			
Echocardiography		X	X	X	X
Angiographic data		X			
ECG		X	X	X	X
HRV measurement		X		X	X

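### The second follow-up HRV recording is set at six months in two places and at 12 months in two others, and at 12 months it could not predict clinical events within the one-year follow-up

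*Protocol article*

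**What the plan says.** Four places in the protocol article fix the times of the follow-up HRV recordings.

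- Abstract: "Additional HRV measurements will be performed one and six months from the index event".
- Section 2.3 (HRV Parameters Measured): "Additional HRV measurements will be performed after the index event (at one and six months").
- Section 2.6 (Participation Timeline): "At 1 month and at 12 months after the index event, HRV will be re-assessed". The same paragraph then plans the analysis on that basis: "an eventual correlation with HRV measured during primary PCI, as well as after 1 month and 12 months, will be analyzed".
- Table 1: the row "HRV measurement" is marked at baseline, 1 month and 12 months. The table has columns for enrollment, baseline, hospital stay, 1 month and 12 months, and none for six months.

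Outcome times are given in Section 2.5: "The primary composite outcome and secondary outcomes will be evaluated during the hospital stay, at 1 month and 1 year following admission for STEMI".

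**The concern.** HRV is the exposure under study, so its recording schedule decides which exposure data will exist. As written, nobody can follow all four places: a reader of Section 2.3 would plan a six-month recording, and a reader of Table 1 would plan none. A six-month recording that was not taken cannot be recovered later.

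The two dates also support different questions. A recording taken part-way through follow-up can be tested as a predictor of what happens next. A recording taken when outcome assessment closes cannot, because every event that counts has already happened. Section 2.6 nevertheless plans to relate the primary and secondary outcomes to the 12-month recording alongside the earlier ones, without separating these uses.

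**Working it through.** No sample-size or power figure is involved. The check compares the texts and then makes one subtraction.

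**Follow-up HRV times, by place**

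| Place | First follow-up | Second follow-up |
|---|---|---|
| Abstract | 1 month | 6 months |
| Section 2.3 | 1 month | 6 months |
| Section 2.6, visit sentence | 1 month | 12 months |
| Section 2.6, analysis sentence | 1 month | 12 months |
| Table 1 | 1 month | 12 months |

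All agree on 1 month, and all are compatible with a recording around primary PCI. They disagree only on the second follow-up recording.

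**Can the places be read together?**

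- As three follow-up recordings (1, 6 and 12 months): no place says so. Each gives exactly two follow-up times, and Table 1 has no column for a third.
- As a fault in reading the table: no. Section 2.6 gives 12 months twice in running prose, and the Abstract and Section 2.3 give six months in running prose.
- As superseded text: the article contains no amendment log, and all the statements are current.
- As detail left to a fuller document: no. The article states two incompatible schedules; it does not merely leave one out.

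**Outcome time left after each recording**

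With outcome assessment ending at 12 months (Section 2.5), time remaining = 12 − (month of recording):

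- 1 month: 12 − 1 = 11 months
- 6 months: 12 − 6 = 6 months
- 12 months: 12 − 12 = 0 months

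**What zero remaining time means**

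The primary composite includes death from any cause (Section 2.5). A patient with a 12-month recording has survived to that visit, so no death within follow-up can come after it. Any non-fatal infarction, revascularization or stroke in such a patient came before the recording, and the HRV value may reflect the event rather than foreshadow it. An association found there is retrospective.

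Echocardiography is also marked at 12 months in Table 1, and LVEF and diastolic function are secondary outcomes. A 12-month HRV value can be related to those measurements from the same visit as a cross-sectional association.

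**The case against.** The strongest reply is that the document shows which schedule its visits were built around. Section 2.4 points to Table 1 for the timing of data collection. Section 2.6 is the dedicated timeline, and the outcome visits in Section 2.5 fit the same pattern of hospital stay, 1 month and 12 months. Six months appears only in one sentence of the Abstract and one parenthesis in Section 2.3. This is a fair account of the layout, but it does not settle the matter: Section 2.3 is where the HRV measurement itself is specified, and the Abstract agrees with it.

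The reply is also right that the recording is secondary. The article calls it additional, and the exposure recorded around PCI, the 1-month recording and the outcome times are all consistent.

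A reader might infer several stronger things that the documents do not support:

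- That the main prognostic analysis is compromised. It rests on HRV recorded around PCI, on which the sections do not conflict.
- That six-month and 12-month readings will be pooled under one label. This is a single-center study, and nothing in the text shows both schedules in use.
- That all of the 200 or more patients are affected. That is a ceiling, since deaths and losses before the late visit reduce it by a number the article does not give.
- That a 12-month recording has no analytic use. The cross-sectional use with LVEF or diastolic function remains.

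One could add that the analytic role of a late recording belongs in a fuller analysis plan. That would hold if the article were silent, but Section 2.6 states an analysis, and as stated it cannot be prognostic for clinical events if the recording is at 12 months.

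**Conclusion.** The contradiction is real and current, and it should be corrected. Its scope is narrow: one additional recording, in patients who reach that visit, and the analyses that use it. The consequence is 6 months of remaining outcome time under one schedule and none under the other. The choice therefore decides whether this recording can serve as a predictor of clinical events.

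The conclusion assumes that outcome assessment ends at one year for each patient, as Section 2.5 states. The three-year duration in Section 2.6 describes the study as a whole, and no later outcome visit is mentioned. The documents do not show which of the two dates was intended, and this point takes no position on it. It is a correction worth making, but not one on which the validity of the main analysis depends.

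**What to change.** 1. Reconcile the Abstract, Section 2.3, Section 2.6 and Table 1 to one HRV schedule. Add a six-month column to Table 1 if that date is kept; otherwise correct the Abstract and Section 2.3.
2. Amend the analysis sentence in Section 2.6 so that each follow-up HRV recording is used as a predictor only of events after it, with a landmark at that visit and patients event-free at that point. For the 1-month recording this means events from month 1 to month 12; for a six-month recording, months 6 to 12.
3. State that a recording at the end of follow-up is descriptive, or is related cross-sectionally to LVEF and diastolic function measured at the same visit.

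The cost is one text clarification, carried over to the registry entry if that also gives the HRV times. No extra patients are needed. If six months is kept, staff need a recording occasion that Table 1 does not at present provide.

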### 2.4. Collected Data

The following data will be collected and analyzed:Demographic data (age, sex);Time to primary PCI in relation to chest pain onset;Comorbidities (arterial hypertension, diabetes mellitus, chronic kidney disease, ischemic heart disease, stroke);Cardiovascular risk factors (advanced age, gender, high body mass index, smoking, sedentarism, inflammation);Cardiac rhythm; HRV parameters (time domain, frequency domain, and nonlinear measurements),Biological data (creatine kinase-MB—CK-MB, lactate dehydrogenase—LDH, aspartate transaminase—AST, cardiac-specific troponin, complete blood count, hemoglobin, hematocrit, glycemia, lipid profile, serum urea, and creatinine, estimated glomerular filtration rate using CKD-EPI equation, serum potassium, and sodium, C-reactive protein, N-terminal pro-b-type natriuretic peptide);Left ventricular ejection fraction (LVEF) evaluated at admission, pre-discharge, and during follow-up;Thrombolysis in myocardial infarction (TIMI) flow before and after primary PCI;Type of stent used for primary PCI;GRACE score;SYNTAX score II will be documented if three-vessel coronary disease or left main stem disease.

All data, including patients’ names and the aforementioned data, will be stored in an electronic database available only for study investigators. Collected data in relation to specific timeframes were displayed in Table 1.

### 2.5. Outcomes and Follow-Up

The primary composite outcome will include all-cause mortality and major adverse cardiovascular events (MACE). MACE will include cardiac mortality, fatal and non-fatal myocardial infarction, unplanned target vessel revascularization (TVR), and stroke (ischemic or hemorrhagic).

In addition, several secondary outcomes will be analyzed: (a) all-cause and cardiac mortality; (b) fatal and non-fatal myocardial infarction; (c) unplanned target vessel revascularization; (d) target lesion revascularization (TLR); (e) stroke; (f) hospitalizations for heart failure; (g) ventricular arrhythmias; (h) LVEF and left ventricular diastolic function. Moreover, the primary composite outcome will be evaluated in a high-risk subgroup of patients, such as elderly patients or those with diabetes mellitus/chronic kidney disease.

TVR will be defined as new stenosis requiring PCI or CABG in another part of the coronary artery treated at the index event. TLR will include unplanned PCI or CABG for the same lesion revascularized during primary PCI. LVEF will be measured using two-dimensional transthoracic echocardiography (Simpson methods). At least E/A or E/e prime ratios will be calculated for left ventricular diastolic function. Ventricular arrhythmias will be defined as ventricular fibrillation or sustained ventricular tachycardia documented at electrocardiographic monitoring. The primary composite outcome and secondary outcomes will be evaluated during the hospital stay, at 1 month and 1 year following admission for STEMI. All data regarding the outcomes will be collected from secure medical records.

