In addition to its possible prognostic value, HRV might be used for AMI diagnosis and myocardial ischemia detection. In one study which enrolled patients without known coronary artery disease, a low HRV had an excellent negative predictive value for myocardial ischemia (97%), though sensitivity and specificity were lower (respectively, 71% and 60%) [25]. In another study, the authors reported that low HRV values were significant predictors for obstructive coronary artery disease, even after multivariable adjustment [10]. Moreover, we will try to elucidate the role of HRV assessment for secondary prevention following STEMI by investigating the incidence of MACE, including fatal and non-fatal myocardial infarction and TLR.

HRV was established as a prognostic marker in the case of patients with end-stage kidney disease undergoing hemodialysis. In this regard, a recent meta-analysis showed increased all-cause mortality (HR 1.63, 95% CI, 1.11–2.39) linked, mainly, to lower SDANN and LF/HF ratio values [5]. Similar results are expected to be documented in the case of patients presenting with STEMI.

Instantaneous HRV assessment could be influenced by various intrinsic and environmental factors. Although short-term and ultrashort-term HRV parameters were investigated extensively investigated in clinical studies, these values should not be used interchangeably with long-term 24 h parameters [11].

In the last years, more data became available in favor of HRV measurement with photoplethysmography using various wrist-worn devices [13,26]. These devices could provide an accurate assessment of all HRV parameters, including time domain, frequency domain, and nonlinear parameters. Usually, wearable devices could collect interbeat interval data, further analyzed with software to derive all HRV parameters [13,26]. Hence, we will investigate the utility of wrist-worn-device-derived HRV parameters to identify patients with STEMI at a higher risk of worse outcomes. Additionally, we will provide an eventual tool for the residual risk stratification in AMI patients and LEFV recovery prediction [27]. In addition, the present study will represent a background to support the integration of HRV parameters in remote control algorithms in this subset of patients as a simple and noninvasive measurement.

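### Isolated repeat revascularisation of the treated lesion falls outside the primary composite under Section 2.5, although the component's name and the Discussion would count it

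*Protocol article*

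**What the plan says.** Section 2.5 of the protocol article builds the primary outcome in two steps. First: "The primary composite outcome will include all-cause mortality and major adverse cardiovascular events (MACE"). Then: "MACE will include cardiac mortality, fatal and non-fatal myocardial infarction, unplanned target vessel revascularization (TVR), and stroke (ischemic or hemorrhagic"). TLR is not in that list.

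The same section defines the two revascularisation outcomes. For TVR: "TVR will be defined as new stenosis requiring PCI or CABG in another part of the coronary artery treated at the index event". For TLR: "TLR will include unplanned PCI or CABG for the same lesion revascularized during primary PCI". The secondary outcomes carry them as separate items: "c) unplanned target vessel revascularization; (d) target lesion revascularization (TLR").

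The Abstract also treats TLR as additional to the composite. Its secondary outcomes begin with "individual components of the primary composite outcome, target lesion revascularization, hospitalizations for heart failure".

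The Discussion (Section 4) describes the study as "investigating the incidence of MACE, including fatal and non-fatal myocardial infarction and TLR".

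**The concern.** A target vessel contains the lesion that was treated in it, so a reader who sees TVR in a composite would expect repeat treatment of that lesion to count. Under the Section 2.5 definition it does not. The composite leaves out failure of the lesion that brought the patient into the study and includes a new stenosis elsewhere in the same artery. No reason is given. The Discussion then places TLR inside MACE, and so inside the primary outcome.

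What is at stake is the event status of individual patients on the primary outcome. The analyses in Section 2.7 that use it (logistic regression, ROC curves and c-statistics, and the high-risk subgroups) all inherit whichever reading is applied. If the choice is left open until outcomes are known, it could be made after seeing which version gives the stronger HRV result.

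**Working it through.** The plan states no figure that can be reproduced here. The check compares the definitions.

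**Step 1: do TVR and TLR overlap?** TVR as defined lies in another part of the artery and TLR is at the same lesion. One procedure on one site cannot be both, so the two categories are disjoint.

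**Step 2: what enters the composite?** All-cause death, cardiac death, MI, TVR as defined, and stroke. TLR enters only if it comes with one of these.

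**Step 3: score three patients under each reading.**

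| Patient | TVR by its name | TVR by the Section 2.5 definition | MACE as the Discussion words it |
|---|---|---|---|
| Unplanned repeat PCI of the index lesion; no death, MI or stroke | Event | Not an event | Event |
| Unplanned PCI for a new stenosis elsewhere in the treated artery | Event | Event | TVR not named; the list is partial |
| Repeat PCI of the index lesion together with an MI | Event | Event, through MI | Event |

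Only the first patient changes status between the name and the definition, so the gap concerns isolated TLR.

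**Step 4: does another section resolve it?** The Abstract agrees with Section 2.5 that TLR is separate from the composite. Table 1 lists the primary and secondary outcomes only as blocks. No section says that TVR includes the index lesion.

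**Step 5: size.** Section 2 gives at least 200 patients. The documents give no TLR rate and no expected number of primary events. For illustration only, let *t* be the number of isolated TLRs and *e* the other primary events. The share of a TLR-inclusive composite that Section 2.5 omits is *t*/(*e* + *t*).

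- *t* = 4 (2% of 200), *e* = 24: 4/28 = 14%
- *t* = 8 (4% of 200), *e* = 24: 8/32 = 25%
- *t* = 2 (1% of 200), *e* = 40: 2/42 = 5%
- *t* = 8, *e* = 16: 8/24 = 33%

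Every *t* and *e* here is assumed. The spread from 5% to 33% shows that the share depends on the inputs chosen and that the documents do not fix it.

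**The case against.** The strongest defence is that the operative text is consistent. Section 2.5 gives a MACE list without TLR, names TLR only as a secondary outcome, and is supported by the Abstract. The one dissenting sentence is in the Discussion. It is a partial list that omits stroke, TVR and cardiac death, and it can be read loosely as naming outcomes of interest. An analyst who follows Section 2.5 to the letter gets one answer. That much stands, and it means the Discussion sentence alone would be a small matter. It does not remove the mismatch between the component's name and its definition, which lies within Section 2.5. Nor is this detail that an article leaves to a fuller document, because the article itself chose to define both terms.

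It is also fair to say that no data are lost. TLR is collected and assessed at every outcome time point, so a composite including it can be computed from planned data. Whether to include TLR is partly a design choice.

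A reader might infer two stronger things, and the documents support neither.

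- **That omitting TLR dilutes the HRV association.** This would need HRV to predict TLR. The Introduction cites a trial in reperfused STEMI patients in which HRV was associated with all-cause mortality but showed no differences for other end-points. The Discussion cites a meta-analysis with a hazard ratio of 2.12 for death against 1.46 for cardiovascular events. If HRV tracks lesion failure only weakly, adding TLR could itself weaken the association. The direction is unknown.
- **That a known share of primary events is missed.** Any such percentage rests on assumed counts.

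**Conclusion.** The point holds as a defect in the definition of the primary outcome. As written, isolated repeat revascularisation of the treated lesion is not a primary event, while a new stenosis elsewhere in the treated vessel is. This runs against the component's name and against the Discussion, and nothing in the article reconciles them.

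The conclusion rests on the plain wording of Section 2.5 and needs no assumption about rates. It is limited to TLR without death, MI or stroke. The number of patients affected and the effect on the HRV results cannot be derived from the documents. The case for settling it before outcome analysis is that a primary outcome should have one reading, fixed without knowledge of the results.

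**What to change.** Before outcome analysis, define TVR for the composite as any unplanned repeat PCI or CABG of the vessel treated at the index event, including the target lesion. Keep TLR as a secondary outcome nested within TVR. Align the Abstract, Section 2.5, the Discussion and the registry entry by a dated amendment.

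If leaving out the target lesion was intended, rename the component (for example, non-target-lesion TVR), state the reason, correct the Discussion sentence, and report the composite including TLR as a sensitivity analysis.

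Either route needs a sentence or two and no new data, since TLR is already collected. The cost is a small, documented change to the wording of a registered primary outcome. The amendment should state whether any outcome data had been seen when it was made.
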